##### Intercept surveys

Each site will have a 3-month control period followed by a 9-month implementation intervention period (TERM—Training, Engagement, Resources development, Marketing and promotion), and a maintenance phase (3 months). Evaluation (observation of users/visitors and onsite intercept surveys) will take place each month during the control period (baseline = B), every 3 months during implementation intervention phase (I1, I2, I3), and once during the maintenance phase (M1), see Table 2 and Fig. 2. The control period will include three evaluation points (B1, B2, B3), each occurring over a 10-day period per month (including one weekend). The time series evaluation will enable controlling for variations in equipment access due to weather (seasonal effects). Potential participants (park users in the specified target area) will be approached by trained, clearly identifiable research staff to see if they meet inclusion criteria. They will be provided with a verbal explanation about the study and all ethical considerations and invited to participate in a survey. Interested participants will then be asked to provide a verbal agreement (consent) to participate. Upon verbal consent, a paper survey will be administered by the researcher onsite. If more than one person is in the park during any observation period, the research staff decision of who to approach would be guided by aiming to overall recruit an equal number of men and women. The participants will be eligible to complete only one intercept survey during the baseline and maintenance period. During the intervention period the same participants can be surveyed multiple times.

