##### Sample size calculation for the intercept surveys

Sample size calculations for the intercept surveys as part of aim 2 are based on the expected number of older people who will complete the survey using data from our previous project [22]. We observed 10 older people using the Seniors Exercise Park in a typical week (prior to formal promotion of the newly installed park). We hypothesised that the implementation intervention (TERM) will result in *at least* a twofold increase in the number of older people using equipment at the completion of the intervention phase (I3) compared to baseline (B1,B2,B3), with a 20% attrition rate (proportion of people refusing to be interviewed) during the maintenance phase (M1). Assuming 25% will decline to participate or have previously completed the survey [40], we will aim for a total of 54 intercept surveys (8 at baseline; 34 across I1-I3 and 12 at M1) per site, with an overall sample of 324 interviewees across the six sites. Each data collection period will include an observation period of 10 days (instead of a typical 7-day period as commonly used [35]). Increasing the number of observations days to 10 days will enhance opportunities for the research team to recruit more older visitors to complete the intercept surveys to meet the targeted sample size.

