##### AIM 2—evaluation of the ENJOY Seniors Exercise Park on physical activity and wellbeing

Summary statistics will be used to describe the demographic, socioeconomic, equipment usage and health-related characteristics of Seniors Exercise Park area users at each time point. Data will also be examined and reported relative to the adult general public, based on the distribution of age, marital status, and country of birth (using Australian Bureau of Statistics census data for each local government area). Linear and logistic regression models (with main effects for site, time-point, season and their interaction) will be used to examine the impact of the implementation intervention on physical activity level (primary outcome) and other health user characteristics. Statistical significance of the interaction term will be used to determine if the outcome varied between sites at each intervention time point (I1-I3) or M1 relative to their baseline difference.

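### Aim 2 judges whether sites differed by the significance of an interaction test that, with 8 baseline interviews per site, misses most sustained site differences of up to about 1 SD

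*Protocol article*

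**What the plan says.** The statistical analysis section for Aim 2 specifies "Linear and logistic regression models (with main effects for site, time-point, season and their interaction") for physical activity level, a primary outcome, and for other health characteristics of users. It then gives a decision rule: "Statistical significance of the interaction term will be used to determine if the outcome varied between sites". The rule applies to I1, I2, I3 and M1, each compared with the differences seen before the intervention.

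The data come from the intercept surveys. The section on their sample size plans "a total of 54 intercept surveys (8 at baseline; 34 across I1-I3 and 12 at M1) per site", which comes to 324 for the whole study. That number is built from expected recruitment. No SD, effect size or power is given for any Aim 2 contrast. The Intercept surveys section adds: "The control period will include three evaluation points (B1, B2, B3"). The 8 baseline interviews per site are therefore spread over three monthly evaluations. The same section lets one person be surveyed more than once during the intervention period.

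**The concern.** A rule that settles by significance whether sites varied has two outcomes, and non-significance is the one that points to no variation. That is informative only if the test would usually find a difference worth knowing about. Here each site's change is measured against 8 interviews, and the interaction has many degrees of freedom, so sizeable differences can easily be missed. If the rule is applied time point by time point without adjustment, the opposite error also arises.

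At stake is what the trial can say about consistency across its six parks, which mix metropolitan and regional settings and are meant to inform wider roll-out. A non-significant interaction taken as consistency would claim more than the data can show.

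**Working it through.** **The plan's own figure.** The starting point is 10 users in a typical week ("We observed 10 older people using the Seniors Exercise Park in a typical week"), with 25% not surveyed.
- Baseline: 10 × 0.75 = 7.5, rounded to 8.
- I1-I3, assuming users rise 10, 15, 20: 7.5 + 11.25 + 15 = 33.75, rounded to 34.
- M1: 20 × 0.8 × 0.75 = 12.
- Total: 8 + 34 + 12 = 54 per site, and 54 × 6 = 324.

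The stated numbers reproduce.

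**Assumptions for the power check.** Two-sided alpha 0.05, linear outcome, equal SD, independent interviews, season terms ignored. Cells per site are 8 at baseline (3/3/2 if B1-B3 are separate), 11/11/12 at I1-I3 and 12 at M1. Differences are in SD units.

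**Degrees of freedom.**
- Baseline pooled: (6−1)(5−1) = 20, residual 324 − 30 = 294.
- B1-B3 separate: (6−1)(7−1) = 30, residual 324 − 42 = 282.

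**Sustained difference.** Suppose k of the 6 sites differ by d at every later wave. The noncentrality is λ = d² × k(6−k)/6 × (8 × 46)/(8 + 46). For k = 3 and d = 0.6 this is 0.36 × 1.5 × 6.815 = 3.68. For d = 1 it is 10.22.

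For a separate 5-df test at one time point with n interviews per site, λ = d² × 1.5 × 8n/(8 + n). For d = 0.6 this is 2.50 at n = 11 and 2.59 at n = 12.

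Noncentral-F power, three sites against three:

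| Difference | 30 df | 20 df | 5 df at one time point |
|---|---|---|---|
| 0.6 SD | 12% | 14% | 19% |
| 0.8 SD | 19% | 24% | 32-33% |
| 1.0 SD | 31% | 39% | 49-50% |
| 1.5 SD | 72% | 82% | 88-89% |

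If only one site differs, power at 1.0 SD falls to 17% (30 df) or 21% (20 df), and at 1.5 SD to 40% or 49%. Splitting I1-I3 as 8/11/15 leaves the 20-df and 30-df figures unchanged, because λ depends only on the later total of 46.

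**False positives if read as separate unadjusted tests.** In simulation with no true site difference, the chance of at least one p < 0.05 is about 15% for four 5-df tests. It is about 45% for 20 single site-by-wave coefficients against a reference site.

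**Precision of one site's change.**
- All later waves pooled: SE = √(1/8 + 1/46) = 0.383 SD, so the 95% CI is ±1.96 × 0.383 = ±0.75 SD. Baseline supplies 0.125/(0.125 + 0.0217) = 85% of that variance.
- A single wave of 11 or 12: ±1.96 × √(1/8 + 1/11) = ±0.91 SD, or ±0.89 SD.

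**Would a pooled site × phase test (baseline against all later waves, 5 df) be better?** Three sites against three, full difference 1 SD, with the fraction of it present at I1, I2, I3, M1:

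| Pattern | Planned 20 df | Pooled 5 df |
|---|---|---|
| 1, 1, 1, 1 | 39% | 68% |
| 0, ½, 1, 1 | 62% | 30% |
| ⅓, ⅔, 1, 0 | 48% | 19% |
| 0, 0, 1, 0 | 54% | 8% |

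The pooled test wins for an equal step at every wave and loses for the other three patterns.

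**Pooled over sites.** The time-point contrast compares 6 × 8 = 48 baseline interviews with about 68 to 90 per later time point. It detects about 0.50 to 0.53 SD with 80% power.

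**The case against.** Several objections carry weight.

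- **Large differences would be found.** A reader might infer that the rule returns no variation whatever the truth. The numbers do not support that: a sustained 1.5 SD gap between three sites and three is found 72-82% of the time, and a 1 SD gap confined to I3 is found 54% of the time at 20 df. The omnibus test also uses contrasts among I1, I2, I3 and M1, which do not depend on the 8 baseline interviews.
- **The article does not say non-significance will be reported as sameness.** This is correct, and it does not say that estimates will be left out. An article may leave interval reporting and multiplicity control to a fuller plan. But the criterion itself is stated, and it is significance. That is a choice made in the text, not a missing detail.
- **Between-site heterogeneity is not a listed aim.** This is also correct. Scale-up is tied to the programme's success, not explicitly to equal benefit across parks. A reader might infer that the primary Aim 2 result is in doubt, but this point does not touch it.
- **A test with fewer degrees of freedom looks like the obvious remedy.** It is not a safe one. The intervention runs over nine months with activities ordered differently by site, and the article expects the doubling of users by I3. Late or waning differences are therefore plausible, and there the pooled test does worse.

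What remains is that, on each reading of the rule, significance is an unreliable guide to whether sites varied for sustained differences up to about 1 SD.

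**Conclusion.** The point holds in this limited form. At the planned numbers, a sustained difference of 0.6 to 1 SD between three sites and three is detected 14-39% of the time at 20 df, 12-31% at 30 df and 19-50% by a separate test at each time point. Power becomes adequate only near 1.5 SD, and not even there if a single site differs. A non-significant interaction is thus weak evidence of consistency. Under unadjusted separate testing, a significant result is weaker evidence of variation than it appears.

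The figures rest on an assumed effect range in SD units, alpha 0.05, a linear outcome and independent interviews. Repeat surveys of the same person would reduce the information in the change from baseline. The conclusion concerns between-site variation only.

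**What to change.** Keep the interaction test as planned, but stop using its significance as the criterion. Replace the sentence in the Aim 2 analysis section with text to this effect:

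- Variation between sites will be judged from each site's change from baseline with a 95% CI, and from the between-site SD of change with its interval.
- The interaction test will be reported alongside these, and a non-significant result will not be read as sites not varying.
- The text will say whether the test is one global test or one test per time point, and if the latter, how multiplicity is handled.

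Do not replace the planned test with a pooled 5-df site × phase test.

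The cost is a few lines of wording and no new data. The intervals will be wide: about ±0.75 SD per site with later waves pooled, wider at a single wave, and a between-site SD from six sites will be imprecise. That width is the accurate statement of what the trial can say about consistency across parks.

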##### AIM 3—economic evaluation – social-return-on investment (SROI)

We will conduct an economic evaluation to determine the SROI for the Seniors Exercise Parks funded by the local governments. Based on pilot work, it is hypothesised that Seniors Exercise Park capital / running costs will be off-set by cost savings of older people who use the Seniors Exercise Parks due to the reduction in private and government funded social and health care costs following participation [49]. This potential reduction in social and health care costs may be associated with health benefits connected with participation in the Seniors Exercise Park. The SROI will be blended with a traditional cost–benefit analysis. The benefits will be tailored to social purposes by including wellbeing, leisure and employment opportunities, in addition to social service and health care utilisation. Costs will include the Seniors Exercise Park capital (purchase, installation and setup), implementation (including the cost of training for allied health professionals and seniors champions), running and maintenance costs. The return/benefit will be modelled based on the difference in reported benefits for older people surveyed prior to, and following, participation in the Seniors Exercise Park; benefits will include the impact on wellbeing, leisure and employment opportunity, and private and government funded social and health care utilisation (to be collected as part of the intercept surveys). Investment costs will take a local government perspective, while the social return will take a broader social perspective. All costs and benefits will be costed at market rate and reported in AUD$2025/26. Where market rates are not available, economic modelling from previous related data sets and the literature will be used.

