### Secondary measures

#### Intercept survey with park visitors

##### Users’ physical and health characteristics

Face-to-face intercept surveys (15–20 min) will be conducted at baseline (pre-implementation B1, B2, B3), during the implementation framework (I1, I2, I3), and at the end of the maintenance follow up (M1). Data will be collected during the periodic observation (SOPARC) days. Intercept surveys will provide more in-depth information about Seniors Exercise Park users’ characteristics. The paper-based survey will include a set of questions across various domains similar to previous research [37, 40], as well as validated questionnaires (detailed below). The set of questions will include socio-economic and demographic characteristics of Seniors Exercise Park users (e.g., age group, gender, country of birth, marital status), if they are local residents or visitors, motivation to use the Seniors Exercise Park equipment, how often they visit the park area, social connectedness/engagement with other people at the park area, their general physical activity level and their leisure/recreation activity at the park, and general health and wellbeing. Socio-economic status will be estimated using postcodes to derive the Australian Socio-Economic Indexes for Areas (SEIFA) 2021 Index of Relative Socio-economic Advantage and Disadvantage, where the first and tenth SEIFA decile represents geographical areas with the greatest socioeconomic disadvantage and advantage respectively [41]. Self-reported social and health-care services utilisation (e.g., General Practitioner visits, hospitalisations) for the 3 months prior, as well as leisure activities and occupation details, will also be collected at each time point to provide relevant information for the economic evaluation.

The following validated questionnaires will be used as part of the survey:
*Health-related quality of life* will be assessed using the EQ-5D-5L [42]. The EQ-5D-5L comprises five dimensions (mobility, self-care, usual activities, pain/discomfort and anxiety/depression), as well as an overall self-rated health status (Visual Analog Scale (VAS) 0–100) where a higher score represents better health. The utility score will be used for the economic evaluation.

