##### Economic evaluation – social-return-on investment (SROI)

The information about the cost investment of participating councils will be collected via an online survey or a bespoke template that will be sent to the community of practice committee members (includes the six local government representatives for each Seniors Exercise Park) frequently at various stages during the trial. The following investment information will be collected and assigned a monetary value: capital costs (purchase, installation and setup); implementation costs (e.g., planning meetings, staff recruitment, marketing, communications, education to Australian Health Professionals and community leaders); running costs (e.g., health professionals, administration team, including the training costs for the allied health professionals and seniors champions) and maintenance costs (e.g., equipment maintenance). To complete the SROI analysis, the investment will be compared to the social return, which will include the monetary value of the Seniors Exercise Park via its impact on participant wellbeing, leisure and employment opportunity, and private and government funded social and health care utilisation (via data collected during the intercept interviews).

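### Aim 3 hypothesises that service-cost savings offset the park's costs, but the planned social return also counts wellbeing, leisure and employment and so does not answer it

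*Protocol article*

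**What the plan says.** The hypothesis stands in the Aim 3 part of the protocol article's statistical analysis section: "it is hypothesised that Seniors Exercise Park capital / running costs will be off-set by cost savings of older people" who use the parks. The same sentence gives the source of those savings: "due to the reduction in private and government funded social and health care costs following participation". It names no other source, and the sentence after it again speaks only of social and health care costs.

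The same section then defines the return more widely: "The benefits will be tailored to social purposes by including wellbeing, leisure and employment opportunities, in addition to social service and health care utilisation". The earlier methods section on the economic evaluation agrees with this wider definition: "the investment will be compared to the social return, which will include the monetary value of the Seniors Exercise Park", through wellbeing, leisure, employment and service use together. The cost-benefit element is not described as a separate result: "The SROI will be blended with a traditional cost–benefit analysis".

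The cost side differs as well. The hypothesis speaks of capital and running costs. The analysis is broader: "Costs will include the Seniors Exercise Park capital (purchase, installation and setup), implementation", followed by running and maintenance. Costs are taken from the local government perspective and returns from a wider social one.

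**The concern.** The hypothesis is a statement about service costs: what older users and public funders no longer spend on social and health care covers what the park costs. The described result is a statement about total social value. One cannot be read off the other, because a favourable social return may come largely or wholly from monetised wellbeing, leisure or employment.

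The distinction matters to the intended audience. The Discussion expects knowledge of the investment relative to its social return to influence council decisions on outdoor spaces. That service savings cover the cost and that social value exceeds the cost are different messages to a funder. With the hypothesis and the SROI in the same section and nothing linking or separating them, a reader of the final report could take the second as evidence for the first.

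**Working it through.** Aim 3 states no numerical figure, so there is nothing of the plan's own to reproduce. The check is algebraic, with assumed values only as illustration.

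**Definitions**

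- S = savings in social and health care costs
- N = monetised wellbeing + leisure + employment
- I = full investment (capital, implementation, running, maintenance)
- C = capital + running costs only, so C ≤ I

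**The two quantities side by side**

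| | Benefit side | Cost side | Quantity |
|---|---|---|---|
| Hypothesis as worded | S | C | S/C ≥ 1 |
| Same idea, full investment | S | I | S/I ≥ 1 |
| Result described | S + N | I | SROI = (S + N)/I |

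**Step 1: benefit side, on the common cost base I.** SROI − S/I = N/I. If N ≥ 0, the SROI is never below S/I. An SROI above 1 needs only S + N > I, so it does not imply S ≥ I.

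**Step 2: illustration with I = 1.00 (assumed values).**

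| S | N | SROI = (S + N)/1.00 | S/I |
|---|---|---|---|
| 0 | 0.5 | 0.5 | 0 |
| 0 | 1.2 | 1.2 | 0 |
| 0 | 2.0 | 2.0 | 0 |
| 0.5 | 0.7 | 1.2 | 0.5 |

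The second and fourth rows have the same SROI. In one there are no service savings, and in the other they cover half the investment. The SROI alone cannot tell them apart.

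**Step 3: how large an SROI would be needed.** If non-service items make up a share w of the return, S/I = (1 − w) × SROI. For S/I to reach 1, the SROI must be at least 1/(1 − w):

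- w = 0.5: 1/0.5 = 2.0
- w = 0.6: 1/0.4 = 2.5
- w = 0.8: 1/0.2 = 5.0

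The share w is not in the documents. These values show only how the required SROI moves with it.

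**Step 4: cost side.** Because C ≤ I, S/C is at least S/I when S ≥ 0. For S > 0, S/C exceeds the SROI when N < S(I − C)/C. If the non-service items were small, the hypothesis as literally worded could therefore hold with an SROI below 1. The wider benefit list pushes the SROI above the quantity in the hypothesis, and the wider cost base pushes it below. Without figures the net direction against the literal wording cannot be fixed. On a common cost base it is one-sided, as in Step 1.

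**The case against.** The best defence is that Aim 3, as stated in the Background and the Study objectives, is to evaluate the social return on investment, and the benefit definition serves that aim consistently in both economic sections. On this view the hypothesis sentence is background from pilot work. Service use is also a listed benefit item and is collected at each survey point, so a fuller economic plan, not shown here, may well report the return by component.

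Much of this stands. A broad SROI is a legitimate main result, and the inputs for a service-only figure are already planned. What does not stand is that the mismatch is mere omitted detail. The article writes down both the hypothesis and the return, and they measure different things.

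Three stronger readings are tempting but unsupported:

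- **That the plan treats an SROI above 1 as confirmation.** No threshold or decision rule is given. Taking 1 as the point of offset is only the usual meaning of the word.
- **That health gains are counted twice.** The survey section says of the EQ-5D-5L, "The utility score will be used for the economic evaluation", while the benefit list has a single wellbeing item. Nothing states two valuations, and one valuation through EQ-5D-5L fits the text equally well.
- **That the service component is too imprecise to be useful.** The documents give no utilisation rates or variances. Precision is in any case a separate question, and would be the same if hypothesis and result matched.

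**Conclusion.** The point holds in a limited form. The Aim 3 hypothesis concerns service-cost savings against capital and running costs. The described result is a wider social return against a wider cost base, and it can exceed 1 with little or no service-cost saving. As described, it does not answer the hypothesis.

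The size cannot be computed, because the documents give no cost or benefit values. On a common cost base the gap between the two ratios is exactly N/I. The claim that the mismatch then favours apparent confirmation assumes that the wellbeing, leisure and employment items are together not negative. The conclusion rests on the article alone, and a fuller economic plan might already contain a service-only result.

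Aim 3 does not carry a primary outcome, so the trial's main inferences are unaffected. It is nonetheless a named aim with its own hypothesis, and the correction is cheap.

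**What to change.** In the Aim 3 statistical section, take one of two routes.

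1. **Add a result that answers the hypothesis.** Pre-specify service-cost savings alone divided by costs, with an uncertainty interval. Give it on two denominators: the full investment (capital, implementation, running and maintenance), and capital plus running costs as the hypothesis words it. For the second, state where training costs belong, since the methods section puts them under running costs and the statistical section under implementation. Keep the full SROI as the main Aim 3 result, itemise it by component, and state that it will not be cited as evidence that service savings offset the costs.
2. **Or reword the hypothesis** so that it refers to the full social return and the full investment.

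The first route costs a few lines and needs no new data, because service use and each cost category are already to be collected. Its downside is that the service-only ratio will look less favourable than the full SROI. The second route costs one sentence, but gives up the claim about service savings.
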